## Abstract

**Background:**

Over the years, there has been a strong consensus in dentistry that at least two implants are required to retain a complete mandibular denture. It has been shown in several clinical trials that one single median implant can retain a mandibular overdenture sufficiently well for up to 5 years without implant failures, when delayed loading was used. However, other trials have reported conflicting results with in part considerable failure rates when immediate loading was applied. Therefore it is the purpose of the current randomized clinical trial to test the hypothesis that immediate loading of a single mandibular midline implant with an overdenture will result in a comparable clinical outcome as using the standard protocol of delayed loading.

**Methods/design:**

This prospective nine-center randomized controlled clinical trial is still ongoing. The final patient will complete the trial in 2016. In total, 180 edentulous patients between 60 and 89 years with sufficient complete dentures will receive one median implant in the edentulous mandible, which will retain the existing complete denture using a ball attachment. Loading of the median implant is either immediately after implant placement (experimental group) or delayed by 3 months of submerged healing at second-stage surgery (control group). Follow-up of patients will be performed for 24 months after implant loading. The primary outcome measure is non-inferiority of implant success rate of the experimental group compared to the control group. The secondary outcome measures encompass clinical, technical and subjective variables. The study was funded by the Deutsche Forschungsgemeinschaft (German research foundation, KE 477/8-1).

**Discussion:**

This multi-center clinical trial will give information on the ability of a single median implant to retain a complete mandibular denture when immediately loaded. If viable, this treatment option will strongly improve everyday dental practice.

**Trial registration:**

The trial has been registered at Deutsches Register Klinischer Studien (German register of clinical trials) under DRKS-ID: DRKS00003730 since 23 August 2012. (http://www.germanctr.de).

## Background

Edentulism still occurs in elderly people in Germany and all over the world. In Germany, 30.5% of the population between 65 and 74 years are edentulous in the maxilla and/or mandible and 22.5% are completely edentulous [1]. Over the years there has been a strong consensus in dentistry that at least two implants are required to retain a complete denture in the edentulous mandible [2,3]. Indeed, two implants in the interforaminal area have high implant success rates and improve masticatory function [4-6]. In addition, a systematic review on the standard care for an edentulous mandible concluded that there is no strong evidence supporting a single standard of care for the edentulous mandible [7]. For elderly patients with a severely resorbed mandible, the use of implants is considered a medical necessity to retain dentures adequately and to reduce the resorption rate of the residual ridge in the anterior mandible. But as edentulism is often connected to having a low income [8], many patients cannot afford an implant therapy with two implants.

The concept of a single median implant in an edentulous mandible was introduced by Cordioli in 1993 [9] and the first 5-year results were published in 1997 with implant success rates of 100% [10]. A randomized clinical trial with 86 edentulous patients, compared mandibular overdentures retained by one or two implants [11]. Mandibular overdentures retained by a single median implant showed comparable satisfaction and maintenance time with lower component costs and treatment time than conventional two-implant overdentures during an observation time of 12 months. In these investigations, implants were left unloaded during healing. In 2010, Liddelow and Henry reported on a 100% implant-survival rate of immediately loaded implants after 36 months of observation when implants with oxidized surfaces were used [12]. Unfortunately, there was no control group with implants following a conventional healing protocol. However, Kronström *et al*. reported a failure rate of 17.6% after 12 months when immediate loading of a single median mandibular implant was applied [6]. So results of immediate loading of a single median mandibular implant retaining an overdenture are conflicting.

Therefore, the present study is designed to show that implant success is not compromised by immediate loading when a single median implant in the edentulous mandible is used to retain a complete mandibular denture. In addition it is the aim of this trial to show that the quality of life and chewing function can be improved earlier by immediate loading with less pain and discomfort for the patient.

### Objectives

This clinical trial will provide scientific evidence on the suitability of immediate loading of implants in an edentulous mandible. For health and economic reasons, a single median implant in the edentulous mandible is chosen as the most cost-effective treatment having a minimal number of implants. Approving immediate loading of a single dental implant in an edentulous mandible will have an enormous effect on the treatment of edentulous patients who have insufficient function of their complete dentures. As a result of this trial, a low-cost highly effective treatment modality might be established for a large group of edentulous patients in Germany.

## Methods/design

This study was designed as a prospective multi-center randomized controlled clinical trial. It will be conform to the CONSORT statement [13]. The study was designed according to Good Clinical Practice (GCP), the principles of the Declaration of Helsinki (2008) and standards for professional conduct.

A consensus for the study design, including patient treatment, materials used, length and frequency of follow-up visits, was achieved. A detailed study protocol exists. To ensure patient safety, an independent data safety and monitoring board has been installed. The study is monitored by an independent monitor to ensure GCP guidelines. The principal investigator approached eight additional departments of prosthetic dentistry in Germany to participate in the trial. One department refused to participate because of existing pressure of work. The study design was approved by the Ethics Commission of the University Hospital Schleswig-Holstein (processing number: AZ 138/12) as well as the Ethics Commissions of all the other participating centers: Ethics Commission of University Hospital Freiburg, Ethics Commission of Heidelberg University Hospital, Ethics Commission of RWTH Aachen University, Ethics Commission of Ulm University Hospital, Ethics Commission of University Hospital Hannover, Ethics Commission of Ernst-Moritz-Arndt University of Greifswald, Ethics Commission of the Dresden University of Technology and the Ethics Commission of the General Medical Council of the city of Hamburg.

### Participants

Patients wishing to participate in this clinical trial have to meet the following inclusion criteria:

– Provided written informed consent to participate in the trial.

– Edentulous male or female patient between 60 and 89 years.

– No contraindications for implantation.

– Sufficient bone in the anterior mandible to place an implant without augmentation procedures.

– Residual bone height is 11 to 20 mm (Class II or III according to McGarry *et al*. [14]) as the lowest vertical height of the mandible and the vertical bone height in the midline of the mandible is at least 13 mm.

– Despite technically acceptable complete dentures in the mandible and maxilla, the patient is unsatisfied with the retention and/or stability of the mandibular denture while the denture in the maxilla has adequate retention and stability.

– Existing dentures have been worn for at least 3 months to allow adaptation.

– Dentures must have a bilaterally balanced occlusal scheme.

Patients with any of the following conditions will be excluded:

– Edentulous patients aged 60 to 89 years with a contraindication for implantation in the mandible caused by systematic diseases or local bone deficits.

– Patients satisfied with the retention of their mandibular denture or who are unsatisfied with the retention and/or stability of their denture in the maxilla.

– Denture height between base and denture tooth central anterior less than 6 mm.

– Subjects with SCL-90, German version index T-scores of 70 or greater, or with two symptom scale scores of 70 or greater.

– Signs that the patient will be uncompliant and will not participate fully according to the test schedule.

– Participation in any former clinical trial should have been finished for more than 2 weeks.

### Study sites

Prosthetic departments of dental schools in Germany interested in clinical research were informed of the design and the aims of this study. Nine departments decided to participate. Each department designated an investigator responsible for patient examinations and follow-up visits and a clinician responsible for patient treatment (implant placement and second-stage surgery).

### Intervention

Two treatment groups are defined. For the experimental group, the median implant is immediately loaded after placement using a ball attachment and a matrix, which is integrated into the existing denture base intraorally. For the control group, the median implant is left unloaded and allowed to heal submerged for 3 months. The implant is loaded after second-stage surgery using a ball attachment and an intraorally placed matrix.

To avoid bias, randomization is conducted after implant placement and primary implant stability measurement by opening a sealed envelope. Neither the patient nor the study team knows the treatment group at the time of implant placement. Randomization is performed centrally by the trial statistician using block randomization with variable block size and an allocation ratio of 1:1. Stratification is according to the patient’s residual bone height (Class II or III according to McGarry *et al*. [14]) and the study center.

All interventions are conducted according to defined standard operating procedures. During the first calibration meeting, videos demonstrating the clinical und surgical procedures are shown. These are made available to all participating study centers. The first implant placement in each center is supervised by the treatment coordinator of the leading center. Experienced clinicians perform the surgical and prosthetic procedures.

### Outcomes

Implant success according to the modified success criteria of Albrektsson *et al*. [15] has been chosen as the primary outcome of this trial. Secondary outcomes are the earlier improvement in quality of life and chewing function tested using the German version of the oral health impact questionnaire [16] and objective masticatory performance [17].

It is hypothesized that patients with immediate loading will suffer less pain and discomfort during the intervention than patients with second-stage surgery as measured by a questionnaire with a visual analog scale. Prosthetic complications and maintenance interventions, such as adjustment or exchange of retention elements, fracture of the denture base, relining and so on, are recorded and should be comparable in both groups.

Follow-up visits will occur at 1 month and 4, 12 and 24 months after implant loading. In addition, patients in the control group will be examined 1 month after implant placement (Figure 1).

**Figure 1 F1:**
[figure not shown]
Organization chart of trial design.

### Stopping criteria

A patient will be removed from the trial if any of the following occur:

– Any complication during implantation.

– A minimum insertion torque of 30 Ncm and/or a minimum implant stability quotient of 60 is not achieved (the patient will not be randomized and will be treated as the control group).

– An allergic reaction to titanium.

– A serious adverse event related to the implantation.

– Any relevant deterioration in the health of the subject possibly affecting participation in the trial.

– Failure to comply with trial requirements.

– Withdrawal of consent.

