### Sample size

The success rate of a single median implant after 2 years as the primary endpoint of the study is a binomial random variable and success probability is assumed to be 97% in the control group as well as in the experimental group. A maximum inferiority of 7% in the experimental group is regarded as clinically acceptable due to the benefits for these patients, i.e., avoiding the burden of a second procedure, having a stable denture directly after surgery and most probably reduced postoperative pain and discomfort, since the soft tissue of the surgical wound is not loaded with the denture during healing. Under these assumptions, a one-sided test of binomial parameters at a 2.5% significance level has a power of 80% to reveal the non-inferiority of the immediately loaded median implant if the sample size is 148 (74 per group). Taking into account a loss to follow-up rate of approximately 20%, a total of 180 patients (90 per group) was considered necessary [18]. It was assumed that the reasons for loss to follow-up would be random with respect to treatment assignment.

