### Blinding

Due to the obvious visible differences in treatment, it is not possible to blind the investigator or the participating patient.

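### Removing patients for events after randomisation, with no stated follow-up of the implant, can bias the primary comparison in either direction

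*Protocol article*

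**What the plan says.** All places are in the protocol article.

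- **Stopping criteria.** One list governs removal: "A patient will be removed from the trial if any of the following occur". It includes "A serious adverse event related to the implantation", an allergic reaction to titanium, "Any relevant deterioration in the health of the subject possibly affecting participation in the trial" and "Failure to comply with trial requirements". The same list holds the torque and stability threshold, for which "the patient will not be randomized and will be treated as the control group".
- **Intervention.** Allocation comes late in the operation: "randomization is conducted after implant placement and primary implant stability measurement by opening a sealed envelope". The stability threshold therefore acts before allocation, while the reasons quoted above can also act after it.
- **Statistical methods.** The primary analysis covers randomised patients followed for 24 months, together with all patients who had an implant failure.
- **Sample size.** 74 per group are needed and 90 per group are recruited to allow for about 20% loss. "It was assumed that the reasons for loss to follow-up would be random with respect to treatment assignment".
- **Discussion.** The 20% allowance is said to include exclusions under the stopping criteria.
- **Blinding.** "it is not possible to blind the investigator or the participating patient".

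**The concern.** The list mixes two kinds of rule. Criteria checked before the envelope is opened decide who is randomised and do no harm to the comparison. Events after allocation are different: the stated consequence is removal from the trial, not merely a change of care, and nothing is said about recording the implant afterwards.

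Take a patient removed at month 2 for a serious event related to the implantation, with the implant still in place. That patient is neither a 24-month completer nor a known failure, and so drops out of numerator and denominator alike. If the implant is lost at month 4, nothing in the article provides for that being recorded.

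Some of these events plausibly bear on implant loss, and the arms differ in how the implant is loaded. Non-compliance and relevant deterioration are judgements made by staff who know the arm. With an expected failure rate of 3%, a few unseen failures can decide the trial.

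**Working it through.** **Inputs from the article.** Success 97% in both arms, margin 7 points, one-sided 2.5%, power 80%, 74 analysed and 90 randomised per group. The loss allowance is (180 − 148)/180 = 17.8%, or 16 patients per arm. This is an upper value for removals after randomisation, because it also covers ordinary loss and stability exclusions.

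**The plan's own figure.** With the unpooled normal formula, n per group = (z₁₋α + z₀.₈₀)² × 2 × 0.97 × 0.03 / 0.07². This gives 73.4, so 74, at one-sided 5%, and 93.2, so 94, at the stated 2.5%. The figure of 74 is thus not reproduced at the stated level. That is a separate matter; 74 is used below because it is the planned analysis size.

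**Assumed inputs.** True failure at the margin, 10% experimental and 3% control. Let f be the share of true failures that occur unseen after removal, and r the share of non-failing patients removed. The article gives neither.

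**Formula.** Apparent failure rate = p(1 − f) / [p(1 − f) + (1 − p)(1 − r)]. When f = r this equals p, so there is no bias.

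For f = 20% in both arms:

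- r = 0: experimental 0.08/0.98 = 0.0816; control 0.024/0.994 = 0.0241; difference 5.8 points.
- r = 17.8%: experimental 0.08/(0.08 + 0.9 × 0.822) = 0.0976; control 0.024/(0.024 + 0.97 × 0.822) = 0.0292; difference 6.8 points.

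**False-positive rate.** Exact binomial enumeration at one-sided 2.5%, for the unpooled Wald test and the Farrington-Manning score test, 74 per arm:

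| f (both arms) | r | Apparent difference | Wald | Score |
|---|---|---|---|---|
| 0 | 0 | 7.0 | 3.8% | 2.2% |
| 10% | 0 | 6.4 | 5.5% | 3.0% |
| 20% | 0 | 5.8 | 8.0% | 4.3% |
| 20% | 10% | 6.3 | 5.7% | 3.2% |
| 17.8% | 17.8% | 7.0 | 3.8% | 2.2% |
| 20% | 17.8% | 6.8 | 4.2% | 2.4% |
| 10% | 17.8% | 7.6 | 2.7% | 1.6% |

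**Unequal hiding, r = 17.8%.**

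- f = 35% experimental and 17.8% control: difference 5.1 points, error 10.4% / 5.1% (73 analysed per arm).
- f = 17.8% experimental and 50% control: difference 8.2 points, error 2.4% / 1.0% (74 per arm).

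**Fragility.**

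- 2 versus 2 failures in 74 per arm: Wald lower limit 0 − 1.96 × √(2 × 0.0270 × 0.9730/74) = −5.2 points; score statistic 1.969. Both tests pass.
- All 90 per arm, one unseen experimental failure (3 versus 2): Wald limit −5.9 points, pass; score statistic 1.864, fail.
- All 90 per arm, two unseen experimental failures (4 versus 2): Wald limit −7.5 points, fail; score statistic 1.494, fail.

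**The case against.** A reader might infer four stronger things, and the case against each is good.

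1. **That failures after removal are never counted.** The article does not say that data collection stops at removal, and the analysis rule counts all patients with an implant failure without limiting it to failures before removal. Patients whose experimental implant fails leave the trial before retreatment yet are still analysed, so leaving the trial is not the same as leaving the analysis. The article also says that a detailed protocol exists. What remains is that no follow-up after removal is stated.
2. **That the drift is towards non-inferiority.** Keeping known failures while dropping event-free patients raises the apparent failure rates. With r = 17.8% and no failure hidden, the difference widens to 8.3 points and the error falls to 1.7% / 1.0% (75 per arm). If non-compliance gathers among controls, who face submerged healing and a second operation, failures hidden there also widen the difference.
3. **That the list contradicts the random-loss assumption.** That assumption concerns treatment assignment, and equal removal in both arms would fit it. The list makes the assumption doubtful for these removals; it does not refute it.
4. **That implant-related harm is not followed to its outcome.** Nothing in the text says so. The article describes an independent safety board and an early-failure stopping rule. The listed event is also one related to the implantation, and some such events may precede the envelope.

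These objections limit direction, size and certainty. They do not touch the core: removal after randomisation is a stated rule, the stated analysis set has no place for a removed patient without a known failure, and an analysis plan cannot recover outcomes that were not collected.

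**Conclusion.** The point holds as a conditional risk of bias. Bias towards non-inferiority requires removed patients to fail more often than retained ones. That is plausible for events related to the implantation, especially in the experimental arm, and open for health decline and non-compliance.

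The size cannot be fixed from the document. Hiding 20% of failures in both arms roughly doubles the false-positive rate only if no non-failing patient is removed. If non-failing patients are removed at the full 17.8%, the rate barely moves, and at 10% hidden it falls below baseline. All of this assumes true failure of 10% versus 3%, 74 analysed per arm, and shares f and r that the article does not give.

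The fragility result needs no assumed removal shares, only an illustrative 2 versus 2 outcome: with up to 16 patients per arm in the loss allowance, one or two unseen experimental failures are enough to overturn it.

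**What to change.** - **Stopping criteria.** Split the list. Criteria applied before the envelope is opened mean that the patient is not randomised, and they are not invoked later. For events after randomisation, care is left to clinical decision, but implant status against the success criteria is still recorded at the existing visits to 24 months. Only withdrawal of consent to data collection, or death, ends this.
- **Statistical methods.** Include these patients in the primary comparison under their allocated arm. For outcomes still missing, a tipping-point analysis would show how many unseen failures would change the conclusion.
- **Sample size.** Limit the random-loss assumption to the losses that remain.

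The cost is a short amendment. No new visits or procedures are needed, and recruitment was still open when the article was submitted. The downside is some effort to obtain an implant-status record from non-compliant or unwell patients.

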### Sample size

The success rate of a single median implant after 2 years as the primary endpoint of the study is a binomial random variable and success probability is assumed to be 97% in the control group as well as in the experimental group. A maximum inferiority of 7% in the experimental group is regarded as clinically acceptable due to the benefits for these patients, i.e., avoiding the burden of a second procedure, having a stable denture directly after surgery and most probably reduced postoperative pain and discomfort, since the soft tissue of the surgical wound is not loaded with the denture during healing. Under these assumptions, a one-sided test of binomial parameters at a 2.5% significance level has a power of 80% to reveal the non-inferiority of the immediately loaded median implant if the sample size is 148 (74 per group). Taking into account a loss to follow-up rate of approximately 20%, a total of 180 patients (90 per group) was considered necessary [18]. It was assumed that the reasons for loss to follow-up would be random with respect to treatment assignment.

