### Statistical methods

For the primary outcome, the measure for non-inferiority of the success rate of the experimental group compared to the control group will be tested by a one-sided equivalence test for the success parameter of the underlying binomial distributions. The significance level for the one-sided equivalence test is 2.5%. All patients that are randomized and followed up for 24 months as well as all patients with an implant failure will be statistically analyzed. The secondary endpoints (improvement of the chewing efficiency and improvement of the oral health related quality of life after the intervention) will be addressed by non-parametric tests for non-inferiority of the experimental group compared to the control group. Non-inferiority of prosthetic complications will be analyzed by one-sided equivalence tests.

In the case of an implant failure in the experimental group, the patient will be treated according to the protocol of the control group with a new implant. Those patients will be excluded from the trial before retreatment. If more than 20% of the implants fail in any group within the first 3 months after implant placement, the study will be terminated. This criterion will be checked every 6 months after the inclusion of the first patient.

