## Discussion

This randomized clinical trial is designed to show the suitability of immediate loading of single median implants in an edentulous mandible. It is hypothesized that there will be non-inferiority of implant success for the experimental group compared to the control group.

Present clinical trials investigating a single midline implant in an edentulous mandible are mostly designed with a small number of patients [6,19,20]. Due to the sample size required for our clinical trial, a multi-center design is necessary. Taking into account a loss to follow-up rate of approximately 20%, a total of 180 patients (90 per group) was considered necessary. The loss to follow-up rate of 20% appears rather conservative but this rate also takes into account the exclusion of patients due to stopping criteria, e.g. compromised implant stability. In one study on immediate loading of a single mandibular implant, only 1 out of 17 implants (5.9%) did not achieve a minimum insertion torque of 30 Ncm [6]. In another study of immediate loading, only 2 out of 27 implants (7.4%) with oxidized surfaces did not achieve an insertion torque of 45 Ncm; however, the insertion torque actually obtained for these two implants was not reported [20]. From these studies, it is assumed that in our trial the number of patients excluded due to compromised implant stability and loss to follow-up will be less than 20%.

In a pilot study conducted at the University of Kiel, 11 patients were treated with one median implant in the mandible [21,22]. During this pilot trial, six implants followed a non-submerged healing protocol and were provided with a healing abutment and thus loaded moderately. No implant failed. The initial idea for the present clinical trial was to design a third treatment group as another experimental group with implants healing unsubmerged and moderately loaded over the healing abutment. However, for this three-arm study design, 354 patients would need to be allocated to the trial, as 282 patients would be needed for analysis. This number of patients would not have been feasible, especially in terms of finance. The idea of the present clinical trial is to compare two different healing protocols and not two different treatment options. The non-inferiority of one versus two implants in an edentulous mandible was shown by Walton *et al*. in 2009 [11]. A third treatment group with two implants in the interforaminal area was thus not considered necessary.

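### Seventy-four patients per group give 80% power at a one-sided 5% level; at the stated one-sided 2.5% level the power is about 70%

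*Protocol article*

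**What the plan says.** All the design inputs are in the Sample size section of the protocol article. On the success rate: "success probability is assumed to be 97% in the control group as well as in the experimental group". On the margin: "A maximum inferiority of 7% in the experimental group is regarded as clinically acceptable". On level and power: "a one-sided test of binomial parameters at a 2.5% significance level has a power of 80% to reveal the non-inferiority", a power said to be reached "if the sample size is 148 (74 per group"). Allowing for about 20% loss, the total is set at 180, or 90 per group. The Intervention section gives 1:1 allocation.

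The Statistical methods section repeats the level for the primary analysis: "The significance level for the one-sided equivalence test is 2.5" per cent. The 2.5% is therefore stated twice, once for planning and once for the analysis.

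The Discussion describes a three-arm design that was considered and dropped, for which "354 patients would need to be allocated to the trial, as 282 patients would be needed for analysis".

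**The concern.** With every input fixed except the test statistic, the sample size should be reproducible. It is reproducible only at twice the stated significance level. The primary test would then be run at one-sided 2.5% on a sample that matches one-sided 5%.

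This does not inflate the false-positive risk. It lowers the chance of showing non-inferiority when it is true. This is the trial's primary hypothesis test, and a reader who relies on the stated 80% would give a failure to show non-inferiority more weight against immediate loading than the design can support. The gap also invites a damaging repair, which is to relax the level to 5% afterwards so that the printed power becomes true.

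**Working it through.** **Inputs** (Sample size section; allocation from Intervention)

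- Success probability 0.97 in both groups, so the true difference is 0
- Margin 0.07, absolute
- One-sided level 0.025, power 0.80
- 74 analysed per group, 1:1

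**Formula.** The article names no formula or test statistic. The standard unpooled normal approximation is

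n per group = 2 × 0.97 × 0.03 × (z₁₋α + z₀.₈₀)² / 0.07² = 0.0582 × (z₁₋α + 0.842)² / 0.0049

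**Reproducing the plan's figure**

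| One-sided level | z₁₋α | (z₁₋α + 0.842)² | n per group | Total analysed |
|---|---|---|---|---|
| 5% | 1.645 | 6.183 | 73.4, so 74 | 148 |
| 2.5% (as stated) | 1.960 | 7.849 | 93.2, so 94 | 188 |

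The printed 74 and 148 are exactly the 5% result.

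**Power at 74 per group**

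Standard error = √(0.0582 / 74) = 0.02804, and 0.07 / 0.02804 = 2.496.

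- At 5%: Φ(2.496 − 1.645) = 80.3%
- At 2.5%: Φ(2.496 − 1.960) = 70.4%

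**Does another method at 2.5% give 74?** Patients per group needed for 80% power:

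| Method | n per group |
|---|---|
| Log relative risk | 87 |
| Unpooled difference | 94 |
| Continuity-corrected difference | 121 |
| Two one-sided tests (full equivalence) | 125 |
| Farrington-Manning score | 136 |
| Arcsine | 180 |
| Pooled comparison, 97% v 90% | 194 |
| Log odds ratio | 330 |

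None gives 74. The smallest is 87.

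**Exact check.** About 2 failures per group are expected (74 × 0.03 = 2.2), so the normal approximation is rough. Enumerating all binomial outcomes at 74 per group, with a nominal one-sided 2.5%:

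| Test | Power, 97% v 97% | Type I error, 90% v 97% |
|---|---|---|
| Unpooled Wald | 70.2% | 3.8% |
| Farrington-Manning score | 53.7% | 2.2% |

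The test that delivers about 70% exceeds its nominal level at this null point. The score test keeps to it there and has about 54% power.

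**Effect of retention.** If all 90 per group were analysed: √(0.0582 / 90) = 0.02543, 0.07 / 0.02543 = 2.753, and Φ(2.753 − 1.960) = 78.6%.

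**Cross-check within the article.** The three-arm design in the Discussion needs 282 analysed patients, and 282 / 3 = 94 per arm, the formula's answer at 2.5%. Allowing 20% loss, 94 / 0.80 = 117.5, so 118 per arm, and 3 × 118 = 354, which is the other figure given there.

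**The case against.** **The formula is inferred.** The article says only that a one-sided binomial test was used and cites a reference that is not at hand. This stands as a point of wording: the 70% should be attributed to the unpooled normal approximation and not to a method the sponsor is known to have used. It does not rescue the figure, since no method tried at 2.5% gives 74 per group.

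**The three-arm figure can be read another way.** Two experimental arms compared with one control could reach 94 per arm by splitting a one-sided 5% over two comparisons. The two-arm 74 would then come from an unsplit 5%, and the 2.5% would be the misdescription. The article does not settle this. The comparison shows that 74 and 94 correspond to different levels, not which level was intended. Because 2.5% is stated for both planning and analysis, it is the level the plan must be held to.

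**The 70% assumes that only 74 per group are analysed.** The plan enrols 90 per group, and the Discussion expects combined exclusions and losses below 20%. So the fair range by the formula is about 70% at 74 to 78.6% at 90. The upper end needs no losses at all and is still short of 80%.

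**The 54% depends on a test that the article does not specify.** This is correct, and the choice of test may properly be left to the analysis plan. The figure shows that 70% is not a lower bound; it does not predict the power of the analysis that will be run.

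**Conclusion.** The stated power is wrong for the stated level. With 97% success in both groups, a 7-point margin, 1:1 allocation and a one-sided 2.5% test, 74 analysed per group give about 70% power by the unpooled normal approximation, not 80%. The chance of missing true non-inferiority is about 30% where the plan implies 20%. With a Farrington-Manning test it would be about 46% (100% − 54%). Eighty per cent power by the unpooled formula needs 94 per group, which is 20 more per group and 40 more in total than planned for analysis.

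The 74 v 94 result rests only on the article's own inputs and the unpooled formula. The 54% rests in addition on the choice of a score test. This must be corrected, because the protocol makes a numerical claim that its own assumptions contradict.

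**What to change.** - Keep the one-sided 2.5% level in both the Sample size and the Statistical methods sections. Do not change it to 5%.
- In Sample size, replace the 80% claim with wording such as: with 74 analysed patients per group, power at one-sided 2.5% is about 70% by the unpooled normal-approximation formula (78.6% if all 90 per group are analysed); 80% would require 94 analysed per group, 188 in total.
- Add that power depends on the test statistic, and that a Farrington-Manning score test would have about 54% at 74 per group. Once the primary test is fixed, quote the power for that test.
- Use the restated power when interpreting a failure to show non-inferiority.

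The cost is one corrected paragraph in the protocol, carried into the analysis plan if it repeats the figure, and a less favourable stated power. No extra patients are needed. If the sponsor wished to keep 80% at 2.5%, the sample would have to grow to 188 analysed, or 2 × 118 = 236 enrolled with 20% loss. The Trial status section shows recruitment still open when the article was submitted.
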